#### Plans to give access to the full protocol, participant-level data and statistical code {31c}

The protocol is available on the ClinicalTrials.gov website (https://clinicaltrials.gov/ct2/show/NCT03368092?term=traumadornase&draw=2&rank=1). Study documents will be de-identified, stored in each recruitment centre and kept for at least 15 years in a locked, secure office, according to French law. All personnel involved in data analysis will be masked. Only the principal investigators and the statisticians will have access to the final data set.

#### Composition of the data monitoring committee, its role and reporting structure {21a}

The data safety and monitoring board (DSMB) will include [name] [name] (drug monitoring specialist), [name] (methodologist and biostatistician), [name] (anaesthesiologist and intensive care physician), [name] (anaesthesiologist and intensive care physician) and [name] (intensive care physician).

The DSMB, independent from the study sponsor and principal investigator, including three intensive care physicians, one methodologist and one drug safety specialist, will meet after inclusion of the first 20 patients to assess the safety of dornase alfa administration in ventilated trauma patients. The safety variables under study are detailed in the “Interventions” section. The DSMB will meet subsequently after further incremental inclusions of 100 patients. The DSMB charter was signed by all of its members.

#### Adverse event reporting and harms {22}

Adverse events and unintended effects of the trial intervention or trial conduct will be declared to the promotor within 24 h of occurrence. Moreover, the DSMB will meet after inclusion of the first 20 patients to assess the safety of dornase alfa administration in ventilated trauma patients. The safety variables under study are detailed in the following. For safety purposes, patient variables will be closely monitored before, during and within the first post-administration hour: lowest SpO_2_, maximal value and maximal increase in peak inspiratory airway pressure, maximal value and maximal increase in plateau airway pressure, extreme values of heart rate and mean arterial pressure, skin erythema, urticaria and variations in central temperature exceeding 1 °C. The DSMB will meet subsequently after further incremental inclusions of 100 patients.

#### Frequency and plans for auditing trial conduct {23}

In every centre, an audit will be performed by the Direction de la Recherche Clinique des Hôpitaux Universitaires de Strasbourg after inclusion of the first patient, then yearly and after enrolment of the last patient.

#### Plans for communicating important protocol amendments to relevant parties (e.g. trial participants, ethical committees) {25}

Important protocol modifications will be communicated to investigators, IRB and trial registries via e-mail. Every protocol amendment will be first submitted to the IRB and, after validation, transmitted to investigating centres, which will acknowledge receipt.

### Dissemination plans {31a}

The results of the study will be released to the participating physicians, referring physicians and medical community no later than 1 year after the completion of the trial, through presentation at scientific conferences and publication in peer-reviewed journals. Eligible authors will meet all four requirements of the ICMJE guidelines:
Substantial contributions to the conception or design of the work; or the acquisition, analysis or interpretation of data for the workDrafting the work or revising it critically for important intellectual contentFinal approval of the version to be publishedAgreement to be accountable for all aspects of the work in ensuring that questions related to the accuracy or integrity of any part of the work are appropriately investigated and resolved

## Discussion

To the best of our knowledge, TRAUMADORNASE is the first large-scale study to evaluate the usefulness of inhaled dornase alfa to reduce the incidence of moderate-to-severe hypoxaemia in a population of severe trauma patients, who will also benefit from other lung-protective measures. The benefits are expected to include a reduction in both duration of mechanical ventilation and stay in the ICU, lower costs of hospital stay, fewer days on mechanical ventilation and a reduction in the selective pressure on multidrug-resistant bacteria.

In order to keep management practices as standardized as possible, we decided to limit the number of investigating centres to seven university-affiliated and non university-affiliated hospitals, all of which are recognized in the field of trauma care and treat more than 50 severe trauma patients per year. These centres belong to the TraumaBase network (www.traumabase.eu), which promotes multicentre clinical research on trauma and ensures consistent recording of clinical data according to the TraumaBase registry guidelines. These seven centres also share the same standards of care and, except for Pitié-Salpêtrière centre, belong to the same region of France (Grand Est).

From a translational point of view, the study will challenge the hypothesis that breaking up the double-stranded DNA backbone of both DAMPs and NETs with dornase alfa may reduce inflammation and NET-induced epithelial and endothelial cell injuries in the lungs of trauma patients.

Dornase alfa is a long-standingFDA-approved mucolytic agent used in cystic fibrosis patients. Its safety profile and limited side effects make it an appropriate candidate to curb DAMP-induced, NET-mediated inflammation. As we will use high-end vibrating mesh nebulizers, which provide excellent lung deposition and drug bioavailability, we expect that dornase alfa will be deposited within the depth of the lung parenchyma, where it may be the most useful.

### Study limitations

The incidence of moderate-to-severe hypoxaemia is the primary study endpoint. A 45% basal incidence of moderate-to-severe hypoxaemia may appear overstated to some experts, but it must be underlined that only severe trauma patients will be included and that a 45% incidence was reported in the last randomized PROMTT trial [13], in the era of damage-control resuscitation [54]. A 15% absolute reduction seems ambitious for a single intervention. However, previous studies using dornase alfa in animal lung injury models and in ventilated patients suffering atelectasis demonstrated striking results [35, 38–41, 55].

Because fluid loading regimens and transfusion strategies are based on local written protocols, they may act as potential confounding variables. However, this will be controlled by the stratification of the randomization at the centre level and adjustment of statistical analyses in cases of differences between groups.

In conclusion, this trial is the first multicentre, randomized controlled, double-blinded study adequately powered to test the hypothesis that aerosolized dornase alfa reduces the incidence of moderate-to-severe hypoxaemia in mechanically ventilated severe trauma patients.

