### Who will take informed consent? {26a}

Inclusion will be feasible after patient approval, relative approval or emergency consent procedure (according to French law [42]).

Subsequent confirmation of consent will be obtained from the relatives and from the patient as soon as possible. The consent forms are available from the corresponding author on request.

After primary haemostasis and emergent surgical interventions, patients will be randomized in the ICU within 6 h. In the case of emergent surgical intervention before ICU admission, a maximum delay of 18 h will be tolerated from hospital admission (trauma bay) to study drug administration. Day 0 will be considered the day of ICU admission.

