### Relevant concomitant care permitted or prohibited during the trial {11d}

#### Standardization of respiratory care

Daily care for the included patients will be protocolized according to good clinical practices, especially concerning respiratory care (semi-recumbent position, protective mechanical ventilation (6–8 ml/kg predicted body weight), PEEP > 5 cmH_2_O, plateau pressure < 30 cmH_2_O, close tracheal cuff pressure monitoring, early enteral feeding (500 ml on day 1), glucose control and protocolized sedation based on both CPOT and RASS scores [46]). Adherence to guidelines will be checked in every centre for every patient.

Patients will be followed until day 30 for the record of study outcomes.

Every concomitant care will be allowed except aerosols during study drug administration.

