### Outcomes {12}

#### Primary endpoint

The primary endpoint will be the incidence of moderate-to-severe hypoxaemia (PaO_2_/FiO_2_ < 200, according to the Berlin definition [5]) in severe trauma patients (ISS > 15) during the first 7 ICU days. The PaO_2_/FiO_2_ ratio will be computed at least once daily (8:00 a.m.) together with the supine chest X-ray and the worst daily PaO_2_/FiO_2_ value will be taken into account to define hypoxaemia severity. In ARDS patients, the severity of hypoxaemia allows for its classification according to the Berlin definition and is strongly associated with mortality, length of recovery and quality of life [6, 7].

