The aim of this study is to show that the frequency of moderate-to-severe hypoxaemia is lower in the dornase alpha group than in the placebo group. The main variable is then dichotomous “moderate-to-severe hypoxaemia yes/no”, modelled in a logistic mixed regression. We will assume that this variable is Bernoulli distributed with parameter π. The logit of this parameter (linear predictor) is additively written as:
$$ \mathrm{logit}\left({\pi}_i\right)={\alpha}_0+{\alpha}_1I\left({g}_i=1\right)+{\beta}_i, $$

where:
*α*_0_ is a grand mean, with mean 0 normal prior (the variance in this normal is 6, corresponding to a low informative prior)*I*(*g*_*i*_ = 1) is a dummy covariate coded for the group of subject *i* (1 for the dornase alpha group and 0 for the placebo group) — the prior on the parameter of this covariate is the same normal as that for the grand mean*β*_*i*_ is a (random) subject effect, on which is assumed a normal prior with mean 0 and low variance (e.g. 10)

Because the linear predictor is on the logit scale, the probability for moderate-to-severe hypoxaemia will be obtained by monitoring the back-transformation of the logit.

This regression model without covariates except group will be completed for taking into account potential confounding variables. In the model, the entire set of these variables will be added and, secondly, selected using stochastic search variable selection (SSVS) [53]. In such a model, the prior distribution on each parameter is a mixture of two mean 0 normal distributions, one with low variance and the other with high variance: if the posterior weight on this second normal is strongly around 0, then the prior on the parameter is essentially driven by a normal distribution whose mean is centred on 0; this is the clue for a “non-significant” parameter.

The secondary analyses will be conducted as the main analysis with a regressive model, testing the difference of a parameter between the two groups. Only the likelihood model will be changed to take into account the type of variable studied: γ distribution for continuous variables such as length of stay and duration of ventilation. Dichotomous variables such as 30-day mortality will be studied with logistic regression.

No statistical procedure for replacing missing values will be used. All variables and subjects will be considered in the descriptive analyses, but, for inference, 20% missing data or more will result in rejection of the variable or individual.

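### The adjustment for fluid loading and transfusion is triggered by an observed arm difference and is not limited to care given before randomisation, so the adjusted model could condition on a consequence of treatment

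*Protocol article*

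**What the plan says.** Under Study limitations, the protocol article states: "Because fluid loading regimens and transfusion strategies are based on local written protocols, they may act as potential confounding variables". It gives two remedies: stratification of randomisation by centre, and "adjustment of statistical analyses in cases of differences between groups".

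The section on statistical methods for primary and secondary outcomes {20a} starts from a logistic model for the primary endpoint with treatment group as the only covariate, plus a subject effect. It then says: "This regression model without covariates except group will be completed for taking into account potential confounding variables". In that extension, "the entire set of these variables will be added and, secondly, selected using stochastic search variable selection (SSVS"). The article does not list the variables or say when they are measured.

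Four other statements bear on timing and on what randomisation already achieves:

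- Section {26a}: "After primary haemostasis and emergent surgical interventions, patients will be randomized in the ICU within 6 h".
- Standardization of respiratory care: "Every concomitant care will be allowed except aerosols during study drug administration".
- Primary endpoint: incidence is counted "in severe trauma patients (ISS > 15) during the first 7 ICU days".
- Trial design {8} and the blinding section {17a}: allocation is stratified by centre and severe traumatic brain injury, and participants, care providers, outcome assessors and analysts are blinded.

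**The concern.** The worry that prompts the adjustment is that local protocols differ. Centres differ, but each centre contributes to both arms under stratified allocation, so its local protocol cannot systematically favour one arm. What remains is the care that individual patients receive.

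Care given before randomisation can differ between arms only by chance, and adjusting for it is legitimate. Care given after randomisation is another matter. With blinding intact, an arm difference there is either chance or something the treatment brought about. A rule that adjusts whenever the arms differ does not separate the two. In the second case it conditions on a consequence of treatment.

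Two things could then go wrong in the extended model. Any part of the effect that acts through fluid or blood product use would be removed, and the estimate would no longer be the overall effect that the primary objective asks about. The estimate could also be biased in a direction that cannot be predicted, because sicker patients tend to receive more fluid and blood and are also more likely to become hypoxaemic.

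**Working it through.** No figure in the documents is at issue, so the main check sets the passages side by side. A simulation then illustrates what adjustment for a post-randomisation variable could do.

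**1. What does the stated rule cover?** The trigger in Study limitations is an observed difference between groups. The extension in {20a} covers the whole set of potential confounders, followed by stochastic search variable selection. Neither contains a limit to pre-randomisation values.

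**2. Could post-randomisation care fall within it?** Patients are randomised in the ICU, dosed on days 0 and 1, and assessed over 7 ICU days with concomitant care otherwise open. Fluids and transfusion during that window are therefore likely. This is an inference, since no section says outright that they continue after randomisation or that their volumes enter the model. Section {26a} also places randomisation after primary haemostasis and emergent surgery, so some resuscitation precedes allocation. The article does not say how much.

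**3. Which estimate is exposed?** Only the extended model. The group-only model contains no such covariate and keeps the full effect. The article does not clearly say which of the two carries the primary conclusion.

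**4. Illustration of size.**

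Inputs from the sample size section {14}: event rates 0.45 (placebo) and 0.30 (dornase alfa), hence a risk difference of 0.45 − 0.30 = 0.15.

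Assumptions not in the documents:
- one normally distributed post-randomisation variable raises the log-odds of hypoxaemia by 0.8 per SD;
- a share s of the log-odds effect runs through it;
- it shares no common cause with the outcome.

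The check used a plain logistic model, without the plan's subject effect, on 1,000,000 simulated patients.

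- Total log-odds effect: ln(0.30/0.70) − ln(0.45/0.55) = −0.847 + 0.201 = −0.647.
- Shift of the intermediate variable under treatment: s × (−0.647)/0.8 SD.
- The direct effect was set so that the overall risks stay at 0.45 and 0.30.
- The adjusted risk difference is standardised over the observed distribution of the intermediate variable.

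| Assumed share s | Shift (SD) | Group-only odds ratio | Adjusted odds ratio | Adjusted risk difference |
|---|---|---|---|---|
| 0% | 0 | 0.525 | 0.479 | −0.150 |
| 25% | −0.202 | 0.523 | 0.565 | −0.117 |
| 50% | −0.404 | 0.526 | 0.668 | −0.083 |
| 75% | −0.606 | 0.523 | 0.778 | −0.051 |

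The loss against 0.150 is 0, 0.033, 0.067 and 0.099. The group-only risk difference stays at about −0.15 in every row. With no common cause in the simulation, only attenuation can appear. It does not quantify the bias that would arise if illness severity drove both fluid use and hypoxaemia.

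**The case against.** The strongest reply is that the sentence in Study limitations speaks of regimens and strategies set by local protocol. These are centre-level practices, and stratification by centre is the first remedy named. On that reading, the second remedy may mean no more than adjusting for chance imbalance in amounts already given, which removes no treatment effect. Covariate lists and measurement times are also commonly left to the full protocol or analysis plan, which are not shown. This reading is possible. What stands against it is that the article states a positive rule whose trigger is an observed arm difference, and that rule as worded admits post-randomisation values.

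Three stronger readings are tempting, and the documents do not support them.

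- *A treatment effect would be adjusted away.* The group-only model is fitted first and is untouched. No section links dornase alfa to lower fluid or transfusion need; the stated rationale concerns inflammation and lung injury. The loss is possible, not established.
- *The rule acts exactly when treatment has changed care.* Chance differences trigger it too.
- *The article contradicts itself on standards of care.* The Discussion says "These seven centres also share the same standards of care", which sits awkwardly beside local fluid and transfusion protocols. Local protocols can still exist within shared standards, and rewording that sentence would change no estimate.

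**Conclusion.** The point holds in a limited form. As written, the adjustment depends on an observed difference between arms and is not confined to pre-randomisation values, although stratified, blinded randomisation already deals with the local-protocol concern behind it. If post-randomisation fluid or transfusion volumes enter the extended model, its estimate could be biased and could lose whatever part of the effect runs through them.

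This rests on two things that the article does not state: that such care continues after randomisation and would be entered in the model, and that treatment might influence it. The size cannot be derived from the documents. The tabulated risk differences illustrate the mechanism under an assumed share, include no loss at all at one end, and are not an estimate for this trial. The sample size and event rates are not affected.

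**What to change.** In Study limitations and in {20a}:

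1. Remove the condition that adjustment follows an observed difference between groups.
2. Allow into the adjusted model only prespecified covariates measured before randomisation: centre, severe traumatic brain injury and, if recorded, fluid and blood product volumes given before randomisation. Any variable selection would work within that set.
3. Report fluids and transfusion after randomisation by arm, descriptively only, and keep them out of the model for the treatment effect.
4. State whether the group-only or the adjusted model carries the primary conclusion.

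The change is one of wording and alters no clinical care, sample size or stated figure. The small cost is that volumes, if used, must be classed as before or after randomisation. The schedule of assessments does not list them by name, so their availability should be confirmed first.

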## Trial status

Protocol version 8.0 was approved by the National Institutional Review Board on 6 November 2018. The study started on 10 March 2019 and is expected to last until September 2022 (36-month inclusion period plus 6-month participation period).

After validation from its Scientific Committee, the TRAUMADORNASE study was funded by the French Ministry of Health.

## Data Availability

Only the principal investigators, the DSMB and the statisticians will have access to the final data set. The data sets used and analysed during the current study will be available from the corresponding author on reasonable request, after publication of the main core article.

## Abbreviations

ARDS: Acute respiratory distress syndrome
ATS: American Thoracic Society
CDC: Center for Disease Control and Prevention
CPOT: Critical Care Pain Observation Tool
DALY: Disability-adjusted life year
DAMP: Damage-associated molecular pattern
DSMB: Data safety and monitoring board
EDTA: Ethylenediaminetetraacetic acid
ELISA: Enzyme-linked immunosorbent assay
FDA: US Food and Drug Administration
FiO_2_: Inspired oxygen fraction
HMGB1: High mobility group box-1
HSP: Heat shock proteins
ICMJE: International Committee of Medical Journal Editors
ICU: Intensive care unit
IRB: Institutional review board
ISS: Injury Severity Score
McMC: Markov chain Monte Carlo
MOF: Multi-organ failure
MRC: Medical Research Council
NE: Neutrophil elastase
NET: Neutrophil extracellular trap
PaO_2_: Partial arterial oxygen tension
PEEP: Positive end-expiratory pressure
qPCR: Quantitative polymerase chain reaction
RAGE: Receptors for advanced glycation end products
RASS: Richmond Agitation and Sedation Scale
SOFA: Sequential Organ Failure Assessment
SSL: Secure Sockets Layer
SSVS: Stochastic search variable selection
TLR: Toll-like receptor
VAP: Ventilator-associated pneumonia
